### Endpoints

The following primary endpoints will be evaluated in this clinical trial: (i) grade of abdominal pain determined using the numeric rating scale (NRS), (ii) grade of abdominal distention determined using the NRS, and (iii) quality of life determined using the Gastrointestinal Quality Life Index (GIQLI) [9]. NRS measurements of abdominal pain and distention will be taken prior to surgery and at postoperative days (POD) 1, 4, 7, 14 and 28. GIQLI will be taken before surgery and at POD 14 and 28.

The secondary endpoints are (i) postoperative nutritional status (Onodera’s prognostic nutritional index (PNI) [10] and Controlling Nutritional Status score (CONUT score) [11]), (ii) time to initial flatus, (iii) time to initial defecation, (iv) bowel gas volume measured using analysis software, (v) character of stool (Bristol Stool Form Scale [12]), (vi) defecation frequency per day, (vii) postoperative complications (Clavien-Dindo classification [13]), (viii) duration of postoperative hospital stay, and (ix) metabolomics analysis of metabolites in stool and blood using gas chromatography-tandem mass spectrometry (GC/MS/MS) and liquid chromatography-tandem mass spectrometry (LC/MS/MS) (Fig. 1).

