### Registration

Patients will be enrolled at POD 1. An eligibility report form will be sent to the registration center (APO PLUS STATION Co., Ltd, Tokyo, Japan). Eligible patients will be centrally randomized to either the DKT group or non-DKT group at the registration center using a computer random number generator with the minimization method for TNM stage, tumor location, and age. Information on the necessary follow-up evaluations will then be sent from the registration center. A flow diagram of this study is shown in Fig. 2.

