### Treatment methods

#### Intervention group: DKT group

DKT (5 g) will be administered orally three times per day between POD 2 and POD 28. DKT manufactured by Tsumura & Co (Tokyo, Japan) will be used. We will monitor adherence by checking the number of doses of DKT that are not administered.

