### Sample size determination

The sample size calculation is based on a primary endpoint, GIQLI. The GIQLI questionnaire containing 36 questions each with five response categories. The responses to questions are summed to give a numerical score (0–128 points). A previous report [9] indicates that the mean ± standard deviation (SD) change in the GIQLI score between two measurements before and 2 weeks after laparoscopic cholecystectomy in 194 patients was 17 ± 20.7 points. Therefore, the clinically significant mean difference in the GIQLI score is set at 20 with a SD of 20. Using a power level of 80% and a two-sided significance level of 5%, 32 patients (16 patients in each group) are required to show a difference between the DKT and non-DKT groups. Therefore, we determined that 40 patients (20 patients in each group) are needed to endure 20% dropout of patients from this trial.

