### Statistical analysis

All analyses will be performed under the intention-to-treat principle. However, patients will be excluded from the analyses if they are proved to be ineligible after enrollment. Both primary and secondary endpoints will be compared between the DKT group and the non-DKT group. A two-tailed *P* value less than 0.05 is considered statistically significant. For continuous variables, the *t* test will be used when continuous variables follow a normal distribution, whereas the Wilcoxon rank-sum test will be used when continuous variables follow a non-normal distribution. For categorical variables, the chi-square test or Fisher’s exact test will be used according to the cell count.

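### Three unranked primary endpoints share one unadjusted 5% threshold with no success rule or primary time point, while the 5% and 80% in the sample size belong to GIQLI alone

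*Protocol article*

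**What the plan says.** All references are to the protocol article.

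- **Endpoints** lists as primary, without ranking them, "grade of abdominal pain determined using the numeric rating scale (NRS), (ii) grade of abdominal distention determined using the NRS, and (iii) quality" of life by GIQLI. On timing it states "NRS measurements of abdominal pain and distention will be taken prior to surgery and at postoperative days (POD) 1, 4, 7, 14 and 28" and "GIQLI will be taken before surgery and at POD 14 and 28".
- **Registration** and **Intervention group** place the start of the comparison: "Patients will be enrolled at POD 1", and the study drug "will be administered orally three times per day between POD 2 and POD 28". The POD 1 scores are therefore pre-treatment.
- **Statistical analysis** says "Both primary and secondary endpoints will be compared between the DKT group and the non-DKT group", by t test or Wilcoxon rank-sum test for continuous variables, and that a two-tailed P "value less than 0.05 is considered statistically significant". It gives no order of testing, division of the 5%, primary day or summary over days.
- **Sample size determination** says "The sample size calculation is based on a primary endpoint, GIQLI". It uses a difference of 20, an SD of 20, 80% power and two-sided 5%, giving 16 per group, raised to 20 per group for 20% dropout. Its only time reference is a published two-week change after laparoscopic cholecystectomy (17 ± 20.7 points, 194 patients).

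**The concern.** A 5% significance level and 80% power describe a trial decided by one test. This trial has three primary endpoints, each held to 0.05, and no statement of how they combine into a conclusion. Both possible rules cause trouble. If one significant endpoint is enough, the risk of a false claim exceeds 5%. If all three are needed, the stated 80% applies to only one of the three hurdles.

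The missing primary day adds to this, because each endpoint has at least two post-treatment assessments from which a result could be chosen. The trial is open-label with no placebo and its primary endpoints are patient-reported. The Discussion already concedes possible bias from the open-label design. A positive result on an endpoint and day that were not fixed beforehand would be hard to defend, and could point the planned full-scale trial at the wrong outcome.

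**Working it through.** **1. Reproduce the plan's own figure.** Inputs from Sample size determination: difference 20, SD 20, two-sided 5%, 80% power, 20% dropout.

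n per group = 2 × (1.960 + 0.842)² × (20/20)² = 15.70, rounded up to 16. Total 32, and 32/0.80 = 40. The stated numbers are reproduced for GIQLI as a single test. The noncentral t distribution gives 78.1% power at 16 per group, with 17 needed for 80%. This small difference is not the issue.

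**2. Count the primary assessments after treatment starts (POD 2).**

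- Pain NRS: POD 4, 7, 14, 28 = 4
- Distention NRS: POD 4, 7, 14, 28 = 4
- GIQLI: POD 14, 28 = 2
- Total: 10

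**3. False-positive risk if any one significant test counts as success and there is no true effect.** For k independent tests, risk = 1 − 0.95^k.

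- k = 3 (one test per endpoint): 1 − 0.95³ = 14.3%
- k = 10 (every assessment tested): 1 − 0.95¹⁰ = 40.1%

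The article gives no correlations, so these are assumed. Simulation of equally correlated normal test statistics (400,000 draws) gives:

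| Assumed correlation | 3 tests | 10 tests |
|---|---|---|
| 0 (exact) | 14.3% | 40.1% |
| 0.3 | 13.7% | 35.1% |
| 0.5 | 12.5% | 28.8% |
| 0.7 | 10.9% | 21.4% |

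With correlation 0.5 within an endpoint and 0.3 between endpoints, ten tests give 32.7%.

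**4. If all three endpoints must be significant.** The false-positive risk does not exceed 5%, but joint power cannot exceed the lowest of the three powers. The article sizes neither NRS scale. As an illustration, assume each scale also had 80% power. Joint power would then run from 0.80³ = 51% (independent) to 80% (perfectly correlated).

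**5. Cost of a simple three-way correction.** Bonferroni level 0.05/3 = 0.0167, standardised difference 1.0, noncentral t:

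| Per group | Power at 0.05 | Power at 0.0167 |
|---|---|---|
| 16 | 78% | 62% |
| 20 | 87% | 74% |

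Restoring 80% would take 23 per group: 46/0.80 = 57.5, so 58 enrolled. With GIQLI at one time as the only primary test, the level stays at 5% and the 40 patients stand.

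**The case against.** A statistical analysis plan, which is not shown, may fix the day for each comparison, a summary over repeated measures and an order of testing. A journal article is also condensed. That stands for those details, and their absence alone would not be a finding. But the article does not leave the threshold open. It names three primary endpoints, holds all of them to 0.05, and gives the whole 5% to one of them in the sample size. A later split of the 5% would conflict with that calculation, as step 5 shows.

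A reader might infer that the plan licenses ten separate tests, any of which makes the trial positive, and so carries a 40% error rate. The article does not support this. The Endpoints section is an assessment schedule. Nowhere is it said that each day is tested separately or that one result suffices. Independence is also implausible for repeated scores from the same patients. Forty percent is a conditional upper bound.

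A reader might also carry the 0.05 threshold over to the metabolite panels and project a count of false positives. The article calls that analysis exploratory, gives no number of metabolites, and does not say that each is tested alone. That extension is not made here.

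Finally, the trial is meant to guide a larger one, and the Discussion admits that the sample may be too small. This lowers the consequence. It does not remove the fault, because the sample size uses conventional confirmatory settings and the limitations do not mention multiplicity.

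**Conclusion.** The point holds as a mismatch between the stated error rates and the stated set of primary endpoints. The firmest figure is 14.3% in place of 5%, for three independent tests if any one suffices. At assumed correlations of 0.3 to 0.7 it is about 14% down to 11%, still about twice the nominal level. Up to 40% (about 21–35% at the same correlations) applies only if every post-treatment assessment is also tested separately. If all three endpoints are required, the level is protected, but 80% is GIQLI's power and not the trial's.

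The sample size arithmetic for GIQLI is sound. The fault is that the article does not define what makes the trial positive. Given the stated aim of guiding a full-scale trial, this should be corrected before analysis but does not invalidate the design.

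**What to change.** Before any analysis by group, amend the protocol or analysis plan and update the registration:

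- Name one primary test: GIQLI change from before surgery to POD 14, at two-sided 5%. This is the endpoint and time closest to the sample-size basis. The article implies POD 14 only through the cited two-week figure, so the sponsor must declare it.
- If that test is significant, test pain NRS, distention NRS and GIQLI at POD 28, in a fixed sequence stated in advance or with Holm. If it is not, report these as estimates with confidence intervals.
- Define one summary for each NRS scale, for example the treatment effect averaged over POD 4 to 28 from a repeated-measures model, in place of a test on each day.

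The cost is wording and a registry update. The sample size stays at 40 and no visits are added. The downside is that the NRS scales lose stand-alone primary status. If the sponsor wants to keep three primary endpoints, the success rule must be stated and the sample size redone for it.

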**Discussion:**

To our knowledge, this is the first randomized controlled trial to investigate the effects of DKT on postoperative subjective outcomes (i.e., postoperative quality of life) following laparoscopic colectomy as primary endpoints. Exploratory metabolomics analysis of metabolites in stool and blood will be conducted in this trial, which previously has only been performed in a few human studies. The study aims to guide a future full-scale pragmatic randomized trial to assess the overall effectiveness of DKT to improve the postoperative quality of life following laparoscopic colectomy.

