## Discussion

This trial will elucidate the effect of DKT on postoperative gastrointestinal symptoms following laparoscopic colectomy in patients with colon cancer. We mainly focus on two important topics: postoperative quality of life and postoperative metabolites in stool and blood.

Although several trials have been conducted, the clinical effectiveness of DKT is still unclear. In previous randomized controlled trials, all primary endpoints were objective outcomes, such as duration to initial flatus and incidence of postoperative paralytic ileus [14–18]. Although some patients were reported to be improved by DKT administration, there has been no report where any subjective outcomes (i.e., postoperative quality of life) are set up as primary endpoints. Assessment of postoperative quality of life has been conducted as a secondary endpoint in some trials, but there was no significant difference between the intervention group and control group [15–18]. This study is the randomized controlled trial to investigate the effects of DKT on postoperative subjective outcomes (i.e., postoperative quality of life) following laparoscopic colectomy as primary endpoints. Moreover, exploratory metabolomics analysis of metabolites in stool and blood will be conducted in this trial. It was reported that DKT could influence the microbiome of stool through bacterial metabolism in animals’ bowels [19, 20]. However, there is no report to date investigating this in humans. Using metabolomics analysis of metabolites in stool and blood, we plan to examine the effect of the intestinal flora by DKT administration, which can lead to the elucidation of the mechanism of DKT in gastrointestinal symptoms and the discovery of the biomarker candidates.

Therefore, we designed this trial to evaluate the effect of DKT on postoperative quality of life and postoperative metabolites in patients with colon cancer undergoing laparoscopic colectomy. The study aims to guide a future full-scale pragmatic randomized trial to assess the overall effectiveness of DKT to improve the postoperative quality of life following laparoscopic colectomy. Methodological rigor, including random allocation and prospective trial registration is aimed at reducing the risk of bias. As a limitation of this study, the possibility of insufficient sample size, bias in the open-label design, and the possibility of unblinding of the assessors to outcome may result in performance bias.

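### Metabolomics is called exploratory but sits among the secondary endpoints under the unadjusted P<0.05 rule, so chance hits are likely to be mixed into the biomarker candidates

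*Protocol article*

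**What the plan says.** Three parts of the protocol article bear on this.

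- **Endpoint status.** The Abstract and the Endpoints section both list metabolites in stool and blood as item (ix) of the secondary endpoints. The Endpoints section describes "metabolomics analysis of metabolites in stool and blood using gas chromatography-tandem mass spectrometry (GC/MS/MS" and adds liquid chromatography-tandem mass spectrometry as a second platform. No number of metabolites is given.
- **Decision rule.** The Statistical analysis section says "Both primary and secondary endpoints will be compared between the DKT group and the non-DKT group". Significance is judged two-sided, by a single cut-off on P: a "value less than 0.05 is considered statistically significant". Normally distributed measurements get a t test and the rest a Wilcoxon rank-sum test. Nothing sets metabolites apart.
- **Purpose and label.** The Abstract says "Exploratory metabolomics analysis of metabolites in stool and blood will be conducted in this trial", and the Discussion repeats the exploratory label. The Discussion also names metabolites as one of the trial's two main topics and expects the work to help explain the mechanism and to lead to "the discovery of the biomarker candidates".

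**The concern.** The label and the rule do not agree. An exploratory screen of many metabolites is normally reported as a ranked list with some measure of how many entries are likely to be false. The only rule in the article treats each secondary endpoint as a single comparison at 0.05. Endpoint (ix) is not a single comparison: it is a panel of unstated size, measured in two matrices on two platforms.

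If the rule is followed metabolite by metabolite, the label *statistically significant* will attach to an unknown mixture of real and chance differences, and readers cannot tell how much is chance. The mechanistic account and the biomarker candidates would rest on that list, and the article says of the whole trial: "The study aims to guide a future full-scale pragmatic randomized trial".

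**Working it through.** **Inputs from the article.** Two-sided 0.05 per test (Statistical analysis); 20 randomized per arm and 20% dropout (Sample size determination).

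**The plan's own figure.** For GIQLI, with difference 20 and SD 20, n per arm = 2 x (1.960 + 0.842)² x (20/20)² = 15.7, rounded up to 16, so 32 in total; 32 / 0.80 = 40. The stated figures reproduce. They matter here only because they give 16 evaluable patients per arm and a planning effect of 20/20 = 1.0 SD. The article gives no error rate for the metabolites.

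**Assumptions.** The panel size m, the number k of metabolites truly shifted and the size of the shift are not in the article. They are varied below.

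**No drug effect.** Expected chance hits = 0.05 x m. Chance of at least one, if tests are independent, = 1 - 0.95^m.

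| m | Expected chance hits | At least one |
|---|---|---|
| 20 | 1.0 | 64% |
| 50 | 2.5 | 92% |
| 100 | 5 | 99.4% |
| 200 | 10 | >99.9% |

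The expected count holds under any correlation between metabolites. The at-least-one figures need independence. With metabolites correlated 0.6 in blocks of ten, the chance is 95% at m = 100 and still above 99% at m = 200.

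**Some true effects.** Expected false hits = 0.05 x (m - k). Expected true hits = k x power of the t test. Approximate false share = false / (false + true).

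| m | k | Shift (SD) | Per arm | False | True | False share |
|---|---|---|---|---|---|---|
| 200 | 10 | 1.2 | 20 | 9.5 | 9.6 | 9.5/19.1 = 50% |
| 200 | 10 | 1.0 | 16 | 9.5 | 7.8 | 9.5/17.3 = 55% |
| 200 | 10 | 0.8 | 16 | 9.5 | 5.9 | 9.5/15.4 = 62% |
| 100 | 10 | 1.2 | 20 | 4.5 | 9.6 | 4.5/14.1 = 32% |
| 50 | 10 | 1.2 | 20 | 2.0 | 9.6 | 2.0/11.6 = 17% |
| 200 | 40 | 1.2 | 20 | 8.0 | 38.4 | 8.0/46.4 = 17% |

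Simulation with t tests on normal data gives average false shares close to these: about 49% for the first row, 30% for the fourth, 16% for the fifth and 17% for the last. The first case gives about 51% with 16 per arm instead of 20, and about 46% with the block correlation above. Independence therefore does not drive the result. A very small panel (m = 20, k = 5, 1.2 SD, 20 per arm) gives about 12%.

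**Benjamini-Hochberg at 10%, m = 200, k = 10.**

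- 1.2 SD and 20 per arm: about 1.0 false and 7.8 true hits (10% false), against 9.6 true hits at P<0.05.
- 1.0 SD and 16 per arm: about 3.2 of 10 true shifts found, against 7.8 at P<0.05.
- 0.8 SD and 16 per arm: about 1.3 of 10, against 5.9.

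**The case against.** The strongest reply is that this is detail for the analysis plan. The Statistical analysis section is a short general summary. A separate plan, which is not shown, may well handle the panel, and the mere absence of a false discovery procedure from an article is no fault. That is correct, and this point does not rest on absence. It rests on a rule that is stated, that reaches endpoint (ix) by its own terms, and that conflicts with the exploratory label elsewhere in the same article. An analysis plan that used false discovery control would depart from the published rule.

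A second reply is that the work is already framed modestly. The Discussion says "exploratory metabolomics analysis of metabolites in stool and blood will be conducted in this trial", speaks only of candidates, and presents the trial as preparation for a larger one. This lowers the stakes, but it does not change the threshold at which a metabolite would be called significant.

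Third, a reader might infer that the panel will yield biomarker candidates by chance alone, or that false discoveries must make up a large share of the list. The article does not support either. The first needs every null hypothesis to be true. Both depend on a panel size that is not stated, and the false share drops to about 16% or 17% in some plausible cases. Nor does the article say that each metabolite gets its own test, or that every metabolite below 0.05 will be named a candidate. That step is a reading of the general rule.

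Finally, strict error control is costly in a trial this small. This objection stands, and it shapes the remedy.

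**Conclusion.** The article contradicts itself on the standing of the metabolomics: exploratory in the Abstract and Discussion, but a secondary endpoint under an unadjusted 0.05 rule in the Endpoints and Statistical analysis sections. If that rule is applied to each metabolite, chance findings are likely to be mixed into the candidates for any panel of about 50 or more. The false share is about 16% to over 50% in the cases with 50 to 200 metabolites. The range rests on assumed panel sizes, numbers and sizes of true shifts, and 16 to 20 evaluable patients per arm. The article fixes only the patient numbers.

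The consequence is confined to the mechanistic and biomarker claims. The primary endpoints, the sample size and the main treatment comparison are not touched. The conflict should be put right, but it does not threaten the trial.

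**What to change.** In the Statistical analysis section, exclude endpoint (ix) from the P<0.05 significance rule and add wording to this effect: metabolite comparisons are exploratory and hypothesis-generating; effect estimates are reported with Benjamini-Hochberg q-values calculated within each matrix (stool, blood); any metabolite named as a candidate is shown with its q-value; and none is called statistically significant on an unadjusted P alone. Make the Endpoints section carry the same exploratory label. Purely descriptive reporting, with no significance claims, would also remove the conflict.

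Do not make q at or below 0.10 a condition for listing a candidate. At 200 metabolites, 10 of them shifted by 1.0 SD, and 16 per arm, only about 3 of the 10 would pass, against about 8 at P<0.05. Reporting q-values without a gate lets readers judge each candidate and keeps weaker signals visible for the later trial.

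The cost is a few sentences and no extra data or patients. The downside is that fewer metabolites can be called significant. The article reports that data are still being collected, so the wording is best settled before the metabolite data are analyzed.

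### The primary endpoints get an unadjusted t or Wilcoxon test picked by the observed distribution, although pre-treatment values are collected: this gives up precision and leaves the effect measure unfixed

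*Protocol article*

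**What the plan says.** The Statistical analysis section compares primary and secondary endpoints between the two groups. Continuous variables get a t test if they follow a normal distribution, "whereas the Wilcoxon rank-sum test will be used when continuous variables follow a non-normal distribution". No covariate is named, neither a baseline value nor a minimization factor. The section does not say whether the final value or the change is tested, or at which time point.

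Under Endpoints, directly after the three primary endpoints are named, the schedule reads: "NRS measurements of abdominal pain and distention will be taken prior to surgery and at postoperative days (POD) 1, 4, 7, 14 and 28". The GIQLI is scheduled before surgery and on POD 14 and POD 28. The POD 1 NRS is not marked as a baseline. It is one, for three reasons:

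- Registration: "Patients will be enrolled at POD 1", with randomization following.
- Eligibility criteria: an NRS of at least 1 on POD 1 is an entry condition.
- Intervention group: the study drug "will be administered orally three times per day between POD 2 and POD 28".

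Under Sample size determination, "the clinically significant mean difference in the GIQLI score is set at 20 with a SD of 20". The source of the SD is a change between "two measurements before and 2 weeks after laparoscopic cholecystectomy in 194 patients was 17 ± 20.7 points".

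**The concern.** Each primary endpoint has a pre-treatment measurement on the same scale, but the stated analysis makes no declared use of it. At about 16 evaluable patients per arm, the standard error of a chance baseline difference is √(2/16) = 0.35 SD, so sizeable imbalances will be common. A model with the baseline as covariate removes that noise using data already in hand. The Discussion itself concedes that the sample may be too small.

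The second issue is the effect measure. A t test addresses a mean difference and a rank-sum test addresses a shift in ranks. The trial is sized on a mean difference. If the data lead to the Wilcoxon test, the primary test no longer addresses the quantity used for sizing. In an open-label trial with patient-reported primary endpoints, that quantity should be fixed before the data are seen.

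**Working it through.** **The plan's own figure.** Difference 20, SD 20, two-sided 5%, power 80%: n = 2 × (1.960 + 0.842)² × (20/20)² = 15.7, so 16 per group, 32 in total. For 20% dropout, 32/0.8 = 40. Both figures reproduce. By the exact noncentral t, 16 per group gives 78.1% power and 17 per group would be needed, which is within the usual tolerance.

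**Inputs for the comparison.** 16 per arm, difference 20 and SD 20 from Sample size determination. The source SD (20.7) belongs to a change score, so SD 20 is read as a change-score SD. The correlation ρ between preoperative and follow-up GIQLI is not given in the document; 0.3 to 0.7 is an assumed range. Equal variance before and after is also assumed.

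**Formulas.**
- Change-score SD = 20.
- Final-score SD = 20/√(2(1−ρ)).
- ANCOVA residual SD = final-score SD × √(1−ρ²) = 20 × √((1+ρ)/2).
- Cost of estimating the slope at N = 32: variance × (1 + 1/28) = 1.036.
- Power: noncentral t with noncentrality (20/SD) × √(16/2); 30 df unadjusted, 29 df for ANCOVA.

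| ρ (assumed) | Final-score SD | Final-score t test | Change-score t test | ANCOVA SD with slope cost | ANCOVA power |
|---|---|---|---|---|---|
| 0.3 | 16.90 | 89.9% | 78.1% | 16.41 | 91.5% |
| 0.5 | 20.00 | 78.1% | 78.1% | 17.63 | 87.3% |
| 0.7 | 25.82 | 56.4% | 78.1% | 18.77 | 83.0% |

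Worked row, ρ = 0.5: 20 × √0.75 = 17.32; × √1.036 = 17.63; noncentrality 20/17.63 × 2.828 = 3.21; power 87.3%.

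**Where the gain ends.** Against a final-score test, ANCOVA breaks even when (1−ρ²) × 29/28 = 1, that is ρ = √(1/29) = 0.19. Against a change-score test the gain shrinks as ρ rises: at ρ = 0.8, ANCOVA has 80.8% against 78.1%.

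**If SD 20 is instead the final-score SD.** The unadjusted final-score test has 78.1%. ANCOVA, before the slope cost, has 81.7%, 88.4% and 96.9% at ρ = 0.3, 0.5 and 0.7.

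**The test-selection rule by itself.** This was simulated with Shapiro–Wilk in each arm, then t or Wilcoxon, 16 per arm, 5,000 runs. Type I error was 4.7% for normal, 5.2% for lognormal and 5.0% for NRS-like data. For normal data with a one-SD shift, power was 78.5% under the rule and 78.6% for the t test always used.

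**The case against.** Several stronger readings are tempting, and the document does not support them.

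- *The plan tests the arms against each other on POD 1.* The Endpoints sentence is a collection schedule that also lists the preoperative score, and no section plans a POD 1 comparison. What stands is that the POD 1 NRS appears among the primary-endpoint measurements without being labelled as baseline.
- *The baselines are ignored.* For the GIQLI this is inference. The sizing rests on a change score, and a t test on change would fit the stated analysis and would use the preoperative value. Even so, ANCOVA has the smaller variance across the assumed range.
- *Choosing the test from the data wastes precision or inflates error.* The simulation shows almost no such effect. With lognormal data and a one-SD shift the rule did better than always using the t test (98.5% against 83.0%). The objection to the rule is the unfixed effect measure only.
- *Adjustment is free.* It costs a little, and its benefit depends on a correlation the document does not give. Requiring an NRS of at least 1 on POD 1 may lower that correlation for the NRS. The power figures here concern the GIQLI only.

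Two further points are fair. An unadjusted test in a randomized trial is valid, because its standard error already allows for chance imbalance. Covariates may also be set out in an analysis plan that is not shown. But the article does not leave the method open: it names an unadjusted two-sample test and a rule for choosing it. A better choice can therefore be recommended without treating missing detail as a fault.

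**Conclusion.** The point holds as one of efficiency and prespecification. It is not an error of validity, and the sample size is not challenged. The named tests take no baseline covariate although suitable pre-treatment values are collected, and the effect measure depends on the observed distribution although the trial is sized on a mean difference.

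Under a change-score SD of 20 and assumed correlations of 0.3 to 0.7, ANCOVA gains about 5 to 13 percentage points of power over a change-score test (91.5 − 78.1 = 13.4; 83.0 − 78.1 = 4.9). Over a final-score test it gains about 2 to 27 points (91.5 − 89.9 = 1.6; 83.0 − 56.4 = 26.6). The 56% figure applies only if final scores are tested, which the article does not state. Below a correlation of about 0.2 nothing is gained over a final-score test. For the NRS the gain cannot be sized from this document.

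**What to change.** Replace the test-selection rule for the primary endpoints with one prespecified baseline-adjusted model each:

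- **GIQLI:** ANCOVA with preoperative GIQLI as covariate at a named primary time point. POD 14 matches the interval used for sizing; POD 28 would be supportive.
- **Pain and distention NRS:** a baseline-adjusted model at one named post-treatment time point, or for the average over POD 4 to POD 28. State that the POD 1 NRS is the baseline and not an outcome occasion.
- **All three:** include the minimization factors (TNM stage, tumor location, age) where the sample size allows. Report the adjusted mean difference with its 95% CI. Keep the Wilcoxon test as a sensitivity analysis that is always reported, not triggered by a normality check.

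The cost is wording, routine programming and a few degrees of freedom, or more if a repeated-measures model is used, which matters at about 32 patients. No new data or patients are needed. The article says data are still being collected, so the change can be made before analysis.
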